## Abstract

**Background:**

Instrumental deliveries are commonly performed in the United Kingdom and Ireland, with rates of 12 – 17% in most centres. Knowing the exact position of the fetal head is a pre-requisite for safe instrumental delivery. Traditionally, diagnosis of the fetal head position is made on transvaginal digital examination by delineating the suture lines of the fetal skull and the fontanelles. However, the accuracy of transvaginal digital examination can be unreliable and varies between 20% and 75%. Failure to identify the correct fetal head position increases the likelihood of failed instrumental delivery with the additional morbidity of sequential use of instruments or second stage caesarean section. The use of ultrasound in determining the position of the fetal head has been explored but is not part of routine clinical practice.

**Methods/Design:**

A multi-centre randomised controlled trial is proposed. The study will take place in two large maternity units in Ireland with a combined annual birth rate of 13,500 deliveries. It will involve 450 nulliparous women undergoing instrumental delivery after 37 weeks gestation. The main outcome measure will be incorrect diagnosis of the fetal head position. A study involving 450 women will have 80% power to detect a 10% difference in the incidence of inaccurate diagnosis of the fetal head position with two-sided 5% alpha.

**Discussion:**

It is both important and timely to evaluate the use of ultrasound to diagnose the fetal head position prior to instrumental delivery before routine use can be advocated. The overall aim is to reduce the incidence of incorrect diagnosis of the fetal head position prior to instrumental delivery and improve the safety of instrumental deliveries.

**Trial registration:**

Current Controlled Trials ISRCTN72230496

## Background

Instrumental deliveries are commonly performed in the United Kingdom and Ireland, with rates of 12 – 17% in most centres [1,2]. Knowing the exact fetal head position is a pre-requisite for safe instrumental delivery. Traditionally, diagnosis of the fetal head position is made on transvaginal digital examination by delineating the suture lines of the fetal skull and the fontanelles [3]. However, accurate diagnosis of the fetal head position by transvaginal digital examination can be unreliable [4].

Malpositions in labour in a vertex-presenting fetus are known to be associated with increased prolonged first and second stages of labour, oxytocin augmentation, use of epidural analgesia, chorioamnionitis, assisted vaginal delivery, third and fourth degree perineal lacerations, caesarean delivery, excessive blood loss, and postpartum infection [5-9]. Trial of instrumental delivery in theatre is twice as likely to fail in occipito-posterior (OP) positions and failed trials are associated with increased neonatal and maternal morbidity and trauma [8,10,11].

We propose a randomised controlled trial to evaluate the use of ultrasound to diagnose the fetal head position prior to attempting instrumental delivery.

The hypothesis is that an abdominal ultrasound scan performed in addition to routine clinical assessment reduces the incidence of incorrect diagnosis of the fetal head position which will reduce the risk of maternal and perinatal morbidity.

### Literature review

A search of Medline from 1965 to 2011 and of the Cochrane Library was undertaken, for relevant systematic reviews, meta-analyses, randomised controlled trials, and other clinical studies. The date of the last search was June 2011. We intend to update this before publishing the results of the trial but at the time of finalising the trial protocol, there were no key changes since the search in June 2011. The main keywords used were: instrumental delivery, vacuum, forceps, fetal position, ultrasound, digital examination, randomised controlled trial. In addition, when reviewing published reference lists, key articles cited were also retrieved and reviewed.

The literature relating to the accuracy of digital vaginal examination versus ultrasound as the gold standard is presented in Table 1. Accuracy varied from 20% to 75% [4,12-19]. The authors of a prospective study of a hundred women which set out to evaluate the learning curves of digital examination and transabdominal ultrasound to determine the fetal head position in labour, reported that it was easier to become skilled in ultrasonography than digital examination [19]. Few studies have addressed error rates in ultrasound determined fetal head position among novice ultrasonographers and only two studies have reported error rates of transabdominal scan within a research setting (6.8% and 7.9% respectively) with another study reporting inability to diagnose the fetal head position in 15% [16,17,19]. We found only two studies evaluating the role of ultrasound assessment to determine the fetal head position before instrumental deliveries [20,21]. Akmal *et al.* compared the accuracy of vaginal examination to transabdominal ultrasound examination in 64 women undergoing instrumental delivery and found that vaginal examination was incorrect in 27% cases with errors being more likely with occipito-posterior positions and if the head was at the level of the ischial spines [20]. Wong *et al.* carried out a randomized trial of fifty women undergoing vacuum extraction for prolonged second stage where women were randomly allocated to either digital examination (n = 25) or digital examination together with transabdominal intrapartum ultrasound (n = 25) prior to vacuum extraction by the attending obstetrician [21]. A midwife measured the distance between the centre of the chignon and the flexion point immediately after delivery. The mean distance between the centre of the chignon and the flexion point was 2.1+/−1.3 cm in the group with digital examination and ultrasound assessment and 2.8+/−1.0 cm in the group with digital examination alone, a small but statistically significant difference [21].

**Table 1 T1:** Studies evaluating accuracy of transvaginal digital examination compared to ultrasound in diagnosing the position of the fetal head in labour

**Author, citation**	**Study design**	**Exposures**	**Outcome measures**	**Results**	**Conclusions**
Akmal S et al. J Matern-Fetal Neo M 2002, 12(3): 172-7	Prospective study 496 women in labour (1^st^ & 2^nd^ stages)	DVE vs TAS (gold standard)	Agreement of DVE within ±45° of TAS correct	DVE in agreement with TAS in 163 cases (49.9%)	Digital examination inaccurate in 50% of cases
Souka AP et al. J Matern-Fetal Neo M 2003; 139(1): 59- 63	Prospective study 148 women in labour (1^st^ & 2^nd^ stages)	DVE vs TAS (gold standard)	Agreement of DVE within ±45° of TAS correct	Accuracy of DVE 31.3% in 1^st^ stage & 65.7% in 2^nd^ stage, more likely to be inaccurate in OP position	Digital examination is less accurate than ultrasound, especially in OP position.
Sherer DM et al. Ultrasound Obst Gyn 2002; 19(3): 258-63	Prospective study 102 women in labour (1^st^ stage)	DVE vs TAS (gold standard)		DVE accurate in 24 cases (24%)	High error rate (76%) with digital examination
Sherer DM et al. Ultrasound Obst Gyn 2002; 19(3): 264- 8	Prospective study 112 women in labour (2^nd^ stage)	DVE vs TAS (gold standard)	Absolute error when DVE not consistent with TAS; and inconsistency of >45°	Absolute error of DVE 65% DVE incorrect by > 45° in 44 cases (39%)	Ultrasound improves accuracy
Dupuis O et al. Eur J Obstet Gynecol Reprod Biol 2005; 123(2): 193-7	Prospective study 110 women in labour (2^nd^ stage)	DVE vs TAS (gold standard)	Agreement of DVE within ±45° of TAS correct	In 20% of the cases, DVE differed significantly (>45°) from TAS, higher in OP & OT positions	Transabdominal ultrasound can increase accuracy
Kreiser D et al. J Matern-Fetal Neo M 2001; 10(40): 283-6	Prospective study 44 women in labour (2^nd^ stage)	DVE vs TAS (gold standard)	DVE & TAS findings compared to actual fetal head position at delivery and restitution of the fetal head – if different, considered to be wrong and quantified as =90°, <90° or >90°	TAS less error than DVE: 6.8% vs 29.6%, *p =* 0.011	TAS is more accurate
Zahalka N et al. AJOG 2005; 193(2): 381-6	Prospective study 60 women in labour (2^nd^ stage)	DVE vs TAS vs TVS	Agreement of DVE within 60° of TAS correct	Discrepancy between DVE & TAS 21.7% Discrepancy between DVE & TVS 23.3% 5 cases where DVE erroneously diagnosed position as being OA when it was OP	TAS and TVS more accurate than transvaginal digital examination
Chou R et al. AJOG 2004; 191: 521- 4	Prospective study 88 women in labour (2^nd^ stage)	DVE vs TAS	DVE & TAS findings compared to actual fetal head position at delivery (direct visualisation of position at vaginal delivery after spontaneous restitution of the head or at caesarean section). Considered correct if DVE/TAS within 45° of actual position.	Accuracy of DVE 71.6% vs 92% accuracy for TAS, p = 0.018	TAS more accurate than DVE
Rozenberg P et al. Ultrasound Obst Gyn 2008; 31(3):332 - 7	Prospective study One novice doing both TAS and VE 100 women (≥ 7 cm dilated)	DVE vs TAS	Learning curve of a novice at diagnosis of the fetal head position by DVE & TAS compared to an expert	Error rate of DVE 50% over first 50cases, down to 28% over last cases vs 8% error with TAS	Learning and accuracy of diagnosis of the fetal head position easier & higher with TAS
Akmal S et al. Ultrasound Obst Gyn 2003; 21(5):437-40	Prospective study 64 women undergoing instrumental delivery	DVE vs TAS	Agreement of DVE within ±45° of TAS correct	Error rate of DVE 26.6% (17 cases), igher for OP and OT	DVE inaccurate in a quarter of cases before instrumental delivery
Wong GY et al.	RCT 40 women undergoing vacuum extraction	DVE vs TAS	Accuracy of vacuum cup placement with respect to the flexion point	Mean distance between chignon & flexion point: 2.1 ± 1.3 cm in DVE + TAS group vs 2.8 cm ± 1.0 cm in VE group (p = 0.039)	TAS improves vacuum cup placement

DVE: Digital vaginal examination.

TAS: Transabdominal ultrasound.

TVS: Transvaginal ultrasound.

OA: occipito-anterior, OP: occipito-posterior, OT: occipito-transverse.

### National survey of current practice

We carried out a questionnaire survey in consultant-led maternity units in the United Kingdom and Ireland to establish the current practice of obstetricians with regards to the assessment of women in labour prior to instrumental delivery [22]. Clinical assessment prior to instrumental delivery, factors associated with difficulty in determining the fetal head position, approaches used to enhance determination of the fetal head position, perceived accuracy rates in assessment of the fetal head position and willingness to participate in a clinical trial of ultrasound assessment of the fetal head position prior to instrumental delivery were explored. There were conflicting opinions on the role of abdominal ultrasound in enhancing determination of the fetal head position prior to instrumental delivery, indicating the need for evaluation within a randomised controlled trial [22]. More than half the obstetricians agreed that there was a need for a trial and would participate in such a trial.

### Validation study

Prior to starting this study, it was important to compare the accuracy of diagnosis of the fetal head position in the second stage of labour by ultrasound scan performed by a novice sonographer and by clinical assessment, to that of an expert sonographer (gold standard); and to evaluate the acceptability of ultrasound in the second stage of labour to women and clinicians [23]. We recruited sixty women who had: (i) an abdominal scan performed by a novice; (ii) an abdominal scan performed by an expert ultrasonographer; and (iii) a clinical assessment performed by an obstetrician or midwife; in the passive second stage of labour. Each assessor was blinded to the findings of the others. The ultrasound findings of the novice and expert ultrasonographer were consistent in 52 (87%) cases for the fetal head position and the novice made no occipito-anterior/occipito-posterior (OA-OP) errors. The clinical diagnosis of the fetal head position was incorrect in 25 (42%) cases with 8 (13%) OA-OP errors [23]. We used these findings as an estimate of the primary outcome for the power calculation, Women and clinicians did not consider the ultrasound assessment to be intrusive. In summary, we found that an abdominal scan by a novice ultrasonographer is an accurate and acceptable method of diagnosing the fetal head position in the second stage of labour [23].

#### Aims and objectives

The aim of this study is to compare routine clinical assessment of the fetal head position alone versus clinical and ultrasound assessment of the fetal head position prior to instrumental delivery.

### The primary outcome is to compare the incidence of incorrect diagnosis of the fetal head position

The secondary outcomes are:

to compare the incidence of neonatal trauma, low Apgar scores, fetal acidosis or admission to the neonatal unit

to compare the incidence of primary postpartum haemorrhage, third and fourth degree perineal tears or prolonged postnatal admission

to compare the incidence of sequential use of instruments, instrumental delivery with more than one operator, failed instrumental delivery, transfer to theatre or caesarean section

to compare the decision-delivery intervals

## Methods

### Recruitment and intervention

Recruitment of women to the study will follow a three stage process.

(1) All potentially eligible women will be given written information about the study in the antenatal clinic. A leaflet and covering letter will explain the trial purpose and design, making it clear that women will only become eligible for the study if they require an instrumental delivery. The leaflet will contain contact details to allow women to discuss the study further if they wish.

(2) Once a woman has presented in early labour or for induction of labour, a research fellow will seek written informed consent if the following criteria are satisfied:

i) the midwife looking after the woman assesses her to be capable of providing informed consent.

ii) the woman has adequate pain control.

iii) the woman has not used systemic opiates in the last four hours.

(3) Once consent has been given the mother will not be consulted again unless she requires an instrumental delivery. After confirmation that all criteria are met, the research midwife/fellow will obtain the allocation.

#### Inclusion criteria

This study will be limited to nulliparous women at term (≥37 weeks' gestation) with singleton cephalic pregnancies, aiming to deliver vaginally who require an instrumental delivery in the second stage of labour.

#### Exclusion criteria

Women with a contraindication to instrumental delivery, or who have a limited understanding of English or are under 18 years of age. Eligibility will also be at the discretion of the responsible obstetrician in cases where there is urgency due to suspected fetal compromise (“fetal distress”).

### Allocation to trial groups

Allocation of eligible women who consent to participate in the trial will be concealed using a fully automated centralised web-based system provided by the Bristol Randomised Trials Collaboration. The randomisation sequence will be created by using block sizes of 4, 8 and 12 and stratified by centre, in a 1:1 ratio for usual care versus intervention.

### Intervention

#### Usual care arm

Women allocated to receive usual care will be managed according to Royal College of Obstetricians and Gynaecologists (RCOG) guidelines and the local hospital protocol [3]. The women will be assessed by abdominal and digital vaginal examination prior to instrumental delivery. Following clinical assessment, location of the fetal occiput in relation to pelvic landmarks will be indicated visually by way of a cross on a data sheet depicting a circle, like a clock, divided into 24 sections, each of 15 degrees (Figure 1). The position will then be classified as OA for direct occipito-anterior, ROA and LOA for right and left occipito-anterior respectively; OP for direct occipito-posterior, ROP and LOP for right and left occipito-posterior; ROT and LOT for right and left occipito- transverse respectively. The obstetrician may then proceed to instrumental delivery. The full clinical assessment, delivery procedure, delivery outcome and measures of early morbidity will be recorded on a standard instrumental delivery proforma. The mother and the neonate will be followed-up until hospital discharge.

**Figure 1 F1:**
[figure not shown]
Data sheet: digital vaginal examination findings.

#### Intervention arm

Women in the intervention group will be managed in the same way. In addition they will receive an ultrasound scan to assess the position of the fetal head and spine. Immediately before or after the clinical examination and before application of the instrument, the fetal head position will be determined sonographically by a trained research fellow. The research fellow will be trained before the start of the trial by a consultant sub-specialist in fetal and maternal medicine and perform a minimum of thirty five ultrasound assessments in the second stage of labour as described in the validation study [23]. For all ultrasound assessments, image- directed pulsed Doppler equipment (Sonosite Titan) with a multifrequency sector array transabdominal transducer, and a 3.5 MHz sector ultrasound probe, will be used.

With the patient in a supine position the ultrasound transducer will first be placed transversely over the maternal abdomen and moved longitudinally to identify landmarks for the fetal spine and head position as described in the validation study [23]. The transabdominal probe is then rotated through 90 degrees, to obtain the transverse view of the fetal spine. Following this, a sliding motion towards the fetal head will be made to obtain a view of the following midline fetal cranial structures: midline cerebral echo, falx cerebri and thalamus and anterior or posterior cranial structures including the orbits and nuchal region. The fetal head position will then be classified as previously described. The obstetrician will be informed of the ultrasound findings to facilitate decision making and may then proceed to instrumental delivery.

### Outcome measures

#### Primary outcome

The primary outcome measure is incorrect diagnosis of the fetal head position. Most errors of clinical diagnosis are where the position is classified as occipito-anterior but is in fact occipito-transverse or occipito-posterior. Incorrect diagnosis of the fetal head position will be established according to any of the following criteria:

i) Position of the head at the time of delivery

If the position of the fetal head was classified as occipito-anterior and is delivered occipito-posterior the diagnosis of the fetal position will be considered incorrect.

ii) Instrument markings on the neonatal head and face

The neonatologist or midwife who attends the delivery will examine the baby. He/she will be asked to record the markings of the instrument on a drawing of the head and lateral aspects of the face (Figure 2). The recorded markings will be used to indicate misplacement of the instrument at a distance from the flexion point (vacuum) or over the face (forceps). If for example the recorded position prior to instrumental delivery was occipito-anterior and the instrument placement suggests an occipito-transverse or occipito-posterior position the diagnosis of the fetal position will be considered incorrect. Furthermore, the diagnosis will be considered incorrect if the markings are more than 45^0^ from the documented fetal head position.

iii) Position at caesarean section

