**Figure 2 F2:**
[figure not shown]
Data sheet: instrument markings on neonatal head and face.

If the delivery is completed by caesarean section the operator will record the position of the head at delivery. If the position of the fetal head was defined as occipito-anterior but is in an occipito-posterior position at caesarean section the diagnosis of the fetal position will be considered incorrect. This information will be cross-referenced with the instrument markings recorded by the neonatologist in cases where there was an initial attempt at instrumental delivery.

The primary outcome will be validated independently by a single investigator who is not involved in scanning or the delivery by reviewing the trial documents (fetal head position recorded by the obstetrician, diagrammatic records of instruments markings on the neonate and documented position of the head position at delivery as described above). Trial allocation will be concealed from this person. Two additional data items will be recorded; i) where the position has been correctly identified the application of the instrument will be classified as optimal or sub-optimal based on the instrument markings and ii) where there is discordance between the findings of the clinician and ultrasonographer the researcher will record whether the ultrasound finding was accepted or not.

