#### Statistical analysis

Data analysis and reporting will proceed according to CONSORT guidelines for randomised controlled trials, and will be conducted blinded to group status by the trial statistician and researcher. The first stage of analysis will be to use descriptive statistics to describe recruited individuals in relation to those eligible, and to investigate comparability of the trial arms at baseline. The primary analysis will involve an intention-to-treat comparison between the two groups for the primary outcome adjusted for stratification/minimisation factors – this will include study centre. Secondary outcomes will be analysed in a similar way. All analyses will use appropriate (that is, logistic or linear) regression models, with results presented as point estimates (odds ratios or difference in means), 95% confidence intervals and p values. Further secondary analyses will involve planned subgroup analyses and will use multivariable regression models with appropriate interaction terms to ascertain any differential effects in relation to, choice of instrument and operator experience.

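### Allocation is concealed from the final validator of the primary outcome but not, as stated, from the staff who make the source records, and the blinded-analysis claim for the researcher does not fit the described data flow

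*Protocol article*

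**What the plan says.** **Who makes the source records.** Under Primary outcome, criterion ii, "The neonatologist or midwife who attends the delivery will examine the baby" and is asked to draw the instrument marks on a diagram of the head and face. These marks can decide the outcome on their own: "the diagnosis will be considered incorrect if the markings are more than 45" degrees from the documented position. For criterion iii, "If the delivery is completed by caesarean section the operator will record the position of the head at delivery". For criterion i, the article does not name the recorder. None of these recorders is said to be masked to arm or to the documented position.

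**Who knows the scan result.** The Intervention arm section states "The obstetrician will be informed of the ultrasound findings to facilitate decision making". The scan takes place close to the clinical examination and before the instrument is applied.

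**Who is masked.** "The primary outcome will be validated independently by a single investigator who is not involved in scanning or the delivery", by reviewing the trial documents, and "Trial allocation will be concealed from this person". The Statistical analysis section adds that analysis "will be conducted blinded to group status by the trial statistician and researcher".

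**What the researcher does.** Where clinician and ultrasonographer disagree, "the researcher will record whether the ultrasound finding was accepted or not". Under Recruitment and intervention, a research midwife or fellow obtains the allocation. Under Intervention arm, a research fellow scans. Under Data management, a researcher completes the case report form and ensures that delivery details are recorded.

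**The concern.** Concealing allocation from the validator protects the step at which records are compared and classified. It does not protect the records themselves. If a person drawing the marks, or recording the position at caesarean, knows the arm or the stated position, that knowledge may shape the record. The validator then reads the result faithfully.

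The risk bears on the primary outcome because criterion ii is its widest route. As worded, criteria i and iii capture only a diagnosis of occipito-anterior that proves to be occipito-posterior. Criterion ii alone captures occipito-transverse errors and the rule of more than 45 degrees, and the Sample size section defines inaccuracy by that same 45-degree difference.

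The second issue is one of accuracy in the text. An analysis described as blinded for a researcher is hard to square with research staff who must know the arm to do their work. A reader could credit the trial with more masking than it has.

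**Working it through.** **1. Masking by role, set side by side**

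| Role | Contribution to the primary outcome | Masking stated? |
|---|---|---|
| Attending neonatologist or midwife | Draws the marks (criterion ii) | None |
| Operator at caesarean | Records head position (criterion iii) | None; the obstetrician is told the scan result in the intervention arm |
| Single validator | Compares the records and classifies | Yes, allocation concealed |
| Statistician | Analyses | Yes |
| Researcher | Records acceptance of a discordant scan; named in the blinded analysis | Yes for analysis, but the item exists only in the scan arm |

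The validator's inputs are the records made in the first two rows. Any distortion in those rows passes through the masked step unchanged.

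**2. The plan's own figure**

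Inputs from Sample size: p1 = 0.20, p2 = 0.10, two-sided alpha 5%, power 80%, 225 per arm.

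- Pooled formula: n = [1.96·√(2·0.15·0.85) + 0.8416·√(0.20·0.80 + 0.10·0.90)]² / 0.10² = (0.990 + 0.421)² / 0.01 ≈ 199 per arm.
- With continuity correction: (199/4)·[1 + √(1 + 4/(199·0.10))]² ≈ 219 per arm.

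The stated 225 is within 3% of the corrected figure. Uncorrected power at 225 per arm is 84.6%. The sample size is not at issue and serves only as the yardstick below.

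**3. Illustration of what distorted drawings could do**

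The documents give no rate of misrecording, so this rate is an assumption. Suppose there is no true effect (20% error in both arms), every error is detected by marks alone, and a fraction d of scan-arm errors is drawn as concordant. The observed scan-arm rate is 0.20·(1 − d). The chance of a significant false benefit at 225 per arm is the normal-approximation rejection probability in that direction, against a nominal 2.5%.

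| d | Observed scan-arm rate | False benefit | Chance of a significant false benefit |
|---|---|---|---|
| 10% | 18% | 2 points | about 8% |
| 20% | 16% | 4 points | about 20% |
| 50% | 10% | 10 points | about 85% |

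At d = 10-20% the shift is 225·0.02 = 4.5 to 225·0.04 = 9 women, or 20-40% of the 10-point target. Half of all scan-arm errors would have to be drawn as concordant to mimic the full design effect. If the planned effect is real, the same d gives 20% versus 0.10·(1 − d) = 9-8%, a shift of 1-2 points.

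**4. Why these are upper figures for a given d**

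Any one of the three criteria is enough to call a diagnosis incorrect. If only a fraction m of errors depends on marks alone, the false benefit is 0.20·m·d. With m = 0.5 (an assumed value) and d = 10-20%, it is 1-2 points. The documents do not give m.

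**5. The blinded-analysis statement**

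Acceptance of a discordant scan can be recorded only for a woman who was scanned, so whoever records it knows her arm. Research staff also obtain the allocation and perform the scan. The Statistical analysis wording is consistent with this only if its researcher is a different person, or if arm codes are hidden from that person at analysis. The article states neither. It uses one undifferentiated title, and the Trial management group section refers to the trial researcher in the singular.

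**The case against.** Five objections carry weight.

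- **The article is condensed.** The Figure 2 form is not shown, and the full protocol may instruct or mask the recorders. This stands as a limit: the article shows that masking is not stated, not that it is absent.
- **Recording is separated from judging.** The person drawing the marks is not asked to decide whether the diagnosis was correct. An independent, masked investigator does that. This is a real safeguard and narrows the room for bias, but it works downstream of the drawing.
- **The size is not sourced, and marks are one route of three.** This stands in full. A reader might infer that the trial would report a spurious 2-4 point benefit for ultrasound. The documents do not support that, because they give no misrecording rate, no share of errors resting on marks alone, and no evidence of direction.
- **The two researchers may not be the same person.** A reader might infer a proven contradiction, or that this researcher records the scan result itself. Neither is shown. The item recorded is whether the finding was accepted, and several research titles appear in the article. Coded arms at analysis could also be compatible with earlier data collection. What remains is a statement that does not fit the data flow without further explanation.
- **The delivery room cannot be fully masked.** True, but it does not prevent a simple instruction or a record of who was aware.

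It would also be wrong to say that only the validator is masked in the trial as a whole, since the statistician is declared blinded too.

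**Conclusion.** The point holds in a limited form. In outcome assessment, the article states concealment only for the validator, while the source records come from attending staff and, at caesarean, the operator, with no masking stated. Masked validation cannot correct a record that was shaped by knowledge of arm or position. The article does not say that the caesarean operator is always the obstetrician who was told the scan result, or that the person drawing the marks knows the arm, so exposure is plausible rather than documented.

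Size and direction cannot be derived. The 2-4 point figure rests on three assumptions: 20% true error in both arms, all errors found by marks, and 10-20% of scan-arm errors drawn as concordant. It falls where criterion i or iii also detects the error.

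Separately, the blinded-analysis statement does not fit the tasks given to research staff unless different people are meant. Both matters are worth correcting because the remedy is cheap and concerns the primary outcome.

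**What to change.** **Marking form (Figure 2).**
- Instruct that the diagram is completed before the recorder sees the position sheet and without being told the arm.
- Where both an attending neonatologist and a midwife are available, use the one who was not present for the scan or examination. Apply the same rule in both arms.
- Add tick boxes for whether the recorder knew the arm and whether the recorder knew the documented position, and report both by arm.
- Label any analysis restricted to unaware recorders as exploratory. Awareness arises after randomisation and may differ by arm, so that subset need not be comparable.

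**Caesarean record.** Acknowledge in the Primary outcome section that the operator's record is unmasked.

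**Statistical analysis section.** Limit the blinded claim to the statistician, working with coded arms and with scan-only items withheld until the primary result is fixed. Keep staff who handle scan data out of outcome coding.

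**Cost.** One form instruction, two tick boxes and a few edited sentences. No extra staff are needed and the sample size does not change. Masking will not always be achievable in the delivery room, which is why awareness needs to be recorded.
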